Our second co-primary outcome, PrEP adherence, is assessed only among those who report initiating PrEP (i.e. taking at least one pill or receiving at least one injection). We assess adherence at 3-, 6-, and 12-month follow-up visits by collecting hair samples to test for the presence of detectable levels of tenofovir, which reflect adherence to either tenofovir disoproxil (TDF) or tenofovir alafenamide (TAF) over approximately the prior month. Samples are ~ 50–100, 1-2 mm-long strands of hair cut with scissors. Samples will be analyzed at the University of California, San Francisco, Hair Analysis Lab for quantification of tenofovir levels [69]. We supplement this biological monitoring with self-reported adherence at all major assessment visits. For injectable PrEP, which involves a monthly intragluteal injection for one month and then bimonthly injections thereafter, optimal adherence will be defined as receipt of injections within one month of their target injection date, which is the time at which people would need to reinitiate monthly injections for two injections (i.e., reload) due to waning drug levels.

Secondary outcome: We assess our secondary outcome, PrEP persistence, using pharmacy and medical records to confirm prescription refill maintenance and attendance at PrEP care follow-up visits. PrEP persistence will be defined as having ≥ 16 days of oral PrEP medication filled per 30-day period, or receiving PrEP injections within one month of their target dates, for at least three-quarters of the months since initiation to study completion (approximately 9/12 months) [76].

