### Sample size calculations

The primary power analysis was based on differences between the PrEP for Health intervention and eSOC conditions in PrEP uptake (co-primary outcome). Effect sizes are estimated from our pilot studies, as well as results of a large mathematical modeling study examining PrEP use among U.S. PWID [87]. Assuming baseline uptake at 25%, with uptake of 50% in the PrEP for Health intervention arm (effect size: d = 0.60), we need 80 completers per condition to have 90% power to find a significant difference at alpha = 0.05. Assuming 20% attrition, we will need to enroll 200 PWID (100 per arm).

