### Limitations

There are potential limitations of the proposed project. First, the RCT may not be powered to determine intervention efficacy for our secondary outcome of PrEP persistence; however, findings may still help inform subsequent research. Second, by situating this study within two urban SSPs in Massachusetts, findings may not generalize to other geographic regions or PWID who do not access SSPs. However, our selected SSP sites cover distinct metropolitan areas and are community-based venues frequented by large numbers of PWID who are diverse in terms of race, ethnicity, age, gender, and sexual orientation, possibly enhancing the generalizability of findings. Moreover, our mediation and moderation analyses will provide more insight into both mechanisms of action and subgroup differences that can inform future broadening in scope. Finally, although this study will not directly address issues of cost-effectiveness of PrEP for PWID, implementation-related findings could inform research on other health interventions for this medically underserved population.

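### Persistence is cut from a monthly coverage record to one yes/no at three-quarters of months, which loses some information in an outcome already conceded to be possibly underpowered

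*Protocol article*

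**What the plan says.** The Measures section assesses persistence, the single secondary outcome, "using pharmacy and medical records to confirm prescription refill maintenance and attendance at PrEP care follow-up visits". Two cuts follow:

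- **Within a month.** The criterion is at least 16 "days of oral PrEP medication filled per 30-day period, or receiving PrEP injections within one month of their target dates".
- **Across months.** The participant is persistent if that criterion is met "for at least three-quarters of the months since initiation to study completion (approximately 9/12 months". A literature source is cited for the definition.

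The result is one yes/no per person. The article mentions no graded version, such as a count or proportion of covered months. The Statistical analyses section names tests and models for uptake and adherence but none for persistence. It does say that GEE will be used and can handle binomial and count outcomes. The Limitations section states that "the RCT may not be powered to determine intervention efficacy for our secondary outcome of PrEP persistence". The sample size rests on uptake alone.

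**The concern.** The records yield a number of covered months for each participant. The three-quarters rule keeps only which side of one line that number falls on. With 12 months since initiation, 8 covered months (67%) and 1 covered month (8%) are both failures, while 9 (75%) and 12 (100%) are both successes. An intervention that moved people from 2 covered months to 7 would show nothing on this outcome.

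A threshold like this usually costs power, and most when few people pass it. The Background reports that evaluations found marked difficulty with adherence and persistence in this population, so a low pass rate is plausible. The authors disclose limited power for persistence, yet the graded information that would recover part of it is already being collected.

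**Working it through.** **1. The plan's own figure.** Inputs from Sample size calculations: "Assuming baseline uptake at 25%, with uptake of 50% in the PrEP for Health intervention arm", 80 completers per arm, 90% power, alpha 0.05 (two-sided, from Statistical analyses).

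Power = Φ{[(p₂−p₁)√n − 1.96√(2p̄q̄)] / √(p₁q₁+p₂q₂)}, with p̄ = 0.375.

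= Φ{[0.25×8.944 − 1.96×0.6847] / 0.6614} = Φ(1.352) = 0.912.

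The stated 90% is reproduced, and 80/0.8 = 100 per arm is exact. No power figure is given for persistence.

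**2. Expected initiators.** 80×0.25 = 20 in the control arm and 80×0.50 = 40 in the intervention arm. The definition counts months from initiation, so these are the people for whom it is defined.

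**3. One case worked by hand.** *Assumed:* the first month is covered; thereafter the monthly chance of stopping for good is h = 0.25 (control) or 0.15 (intervention); 12 months are observed.

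- *Yes/no.* P(at least 9 of 12) = (1−h)⁸ = 0.100 and 0.272. SE = √(0.100×0.900/20 + 0.272×0.728/40) = 0.097. z = 0.172/0.097 = 1.77. Power = Φ(1.77−1.96) ≈ 0.43.
- *Proportion of months.* Mean = [1−(1−h)¹²]/(12h) = 0.323 and 0.477. The SDs from the same truncated geometric distribution are 0.251 and 0.324. SE = √(0.251²/20 + 0.324²/40) = 0.076. z = 0.154/0.076 = 2.03. Power = Φ(2.03−1.96) ≈ 0.53.
- *Information kept by the yes/no.* (1.77/2.03)² ≈ 0.77, a loss of about 23%.

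**4. Range over assumptions, 20 versus 40 initiators.** Information kept by the yes/no relative to the proportion of months; ICC is the assumed within-person correlation between months (0.1 to 0.9).

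| Assumed coverage, control vs intervention | Kept |
|---|---|
| mean 0.5 vs 0.7 | 72-94% |
| mean 0.4 vs 0.6 | 54-92% |
| permanent discontinuation, several rates | 57-92% |
| mean 0.3 vs 0.5 | 32-90% |
| mean 0.2 vs 0.35 | 12-88% |

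The first three rows give the 6% to 46% loss. A loss above half appears only in the last two rows, where coverage is low and months within a person are weakly correlated.

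**5. Power among initiators, by simulation.** *Assumed:* start times concentrated early (mean 2 months), discontinuation hazards varying between people, and 90% of on-PrEP months meeting the fill rule. Pass/fail was tested by chi-square and the proportion of months by Welch t-test.

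| Control monthly hazard | Discontinuation halved: pass/fail vs proportion | Cut to a third: pass/fail vs proportion |
|---|---|---|
| 0.15 | 22 vs 23% | 42 vs 43% |
| 0.30 | 20 vs 27% | 42 vs 52% |
| 0.60 | 14 vs 28% | 35 vs 56% |

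Type I error was near 5% for both tests. The gain is 1 to 21 points. A repeat with slightly different rounding of months gave 21 vs 21% in the first cell, so the lower end is effectively zero. With low coverage and weakly correlated months the gain can be larger: 0.23 against 0.57 at mean coverage 0.2 vs 0.35 and ICC 0.3.

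**6. All randomised, non-initiators scored 0.** With 80 per arm and discontinuation halved, pass/fail against mean covered months is 85 vs 93%, 78 vs 93% and 60 vs 90% at the three hazards. With an effect on uptake only, it is 46 vs 75%, 32 vs 66% and 17 vs 56%. In those uptake-only scenarios persistence after initiation is identical in the two arms, and a plain uptake test has 91% power.

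**The case against.** The strongest defence is that a prespecified, interpretable rule taken from a cited source is a legitimate secondary outcome, and that its limited power is openly disclosed. The article also names no test for persistence, so the chi-square used above is an assumption. A statistical analysis plan that is not shown may already analyse monthly coverage. All of this stands. It makes the point an improvement to the plan and not the correction of an error. It does not change the fact that the outcome is defined as a single yes/no.

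Four stronger readings are tempting, and the document does not support them:

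- *The cut discards most of the information.* This needs persistence rates or month-to-month correlation, and the article gives neither. In many plausible cases the yes/no keeps well over half.
- *The cut is why the outcome is underpowered.* The expected 20 versus 40 initiators are the main cause. With discontinuation halved, power stays below 30% on either scale.
- *Switching to covered months would gain 8 to 39 points.* Those gains (93−85 and 56−17 in step 6) come from moving to all randomised participants with non-initiators at zero. That is a different estimand. When only uptake differs, it is a weaker version of the uptake test and could be misread as evidence of durability.
- *Persistence is the trial's only measure of durability.* Tenofovir in hair is collected at 3, 6 and 12 months, and a longitudinal analysis of adherence over 12 months is planned.

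**Conclusion.** The point holds in a limited form. The definition reduces a graded monthly record to one yes/no, and the yes/no kept less information in every case where the two were compared on that scale. Among initiators the loss is about 6% to 46% at moderate coverage or with permanent discontinuation, and larger if persistence is poor. In the discontinuation scenarios the graded comparison gains about 0 to 20 points of power and was never materially worse. These sizes rest on assumed persistence rates, assumed within-person correlation and the planned 25% and 50% uptake; the direction does not depend on the particular values tried. The statement in Limitations remains correct after the change. This is a low-cost improvement to a secondary outcome and does not affect the co-primary analyses.

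**What to change.** 1. Keep the three-quarters responder rate exactly as defined and report it by arm, so that results can be set beside the cited literature.
2. Base the between-arm persistence comparison on the number of covered 30-day periods out of the months since initiation. Use the same records and the same per-month rule, for example in a binomial GEE with robust standard errors, adjusted for site. With about 20 initiators in one arm, a small-sample correction or bootstrap for the standard error is prudent.
3. If wanted, add covered months (0-12) among all randomised, with non-initiators scored 0, as a supplementary measure. Label it as combining uptake and persistence.
4. Leave the power caveat in Limitations in place.

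The cost is a few sentences in the analysis plan and a few lines of code, with no new data, visits or participants. Recruitment was ongoing and no interim analysis is planned, so the change can be fixed before outcomes are analysed. The one downside is that a proportion of months compares slightly less directly with published persistence rates, which item 1 offsets.

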### Statistical analyses

Planned preliminary analyses include assessing distributions and autocorrelations across time for all variables. As we are utilizing interviewer-administered survey assessments, the primary anticipated reason for missing data is participant attrition. Based on our preliminary studies, we are anticipating and accounting for 20% attrition. Attrition effects will be evaluated by testing whether systematic differences exist between participants who complete the research study and those who discontinue participation. We will explore strategies (e.g., multiple imputation) for imputing missing data based on patterns of missingness, using sensitivity analyses to determine the optimal method of handling missingness. Dependent variables will be examined to determine which distributional models are most appropriate for subsequent statistical procedures. We will examine the equivalence of the random assignment with regards to key baseline characteristics, including socio-demographics and risk behaviors.

Aim 1: Our primary analysis will compare PrEP uptake and adherence (co-primary outcomes) between the PrEP for Health intervention and eSOC conditions. For PrEP uptake, we will perform chi-square tests to examine group differences in proportions over the course of the study, and Cox proportional hazard models to assess differences in time to PrEP initiation. For PrEP adherence, we will initially assess differences in adherence at 3-month follow-up visits. We will also conduct longitudinal analyses to assess differences in adherence over the course of the study (12 months). We will use generalized linear models (GLMs) with properly chosen link functions. GLMs will be estimated using generalized estimating equations with robust standard error estimates (GEE), which provide an extension of regression analysis to the case of correlated or repeated observations and allows for inclusion of both categorical (e.g., binomial) and count-dependent variables (e.g., Poisson, zero-inflated) and appropriate modeling of covariance structures when observations are correlated across time. We will follow an intent-to-treat model, analyzing participants according to the study arm to which they are assigned, regardless of fidelity to assigned group. Sensitivity analyses will compare those who receive the intervention session(s) to those who do not. All analyses will use two-tailed tests of significance, with significance at alpha level 0.05.

Aim 2: For mediation analyses, we will explore the role of hypothesized mediators using structural equation modeling (SEM) to determine whether the intervention impacts PrEP uptake and/or adherence through our hypothesized mediators. SEM will allow for the simultaneous estimation of total, direct, mediated, and indirect effects of the intervention on the outcome(s) via a set of multiple mediators, simultaneously. The fit of the overall model will be assessed, and individual paths will be assessed using path coefficients, standard errors for each path coefficient, and tests of significance of each coefficient [86]. Inferences for indirect effects will be estimated using bootstrapped confidence intervals.

Aim 3: To assess heterogeneity of intervention effects, we will examine interactions between the intervention and hypothesized moderators on both the multiplicative and additive scales. Multiplicative interaction will be estimated by including a treatment x moderator term in primary analyses described in Aim 1 above. Additive interaction will be estimated by calculating the Attributable Proportion due to Interaction (API), the proportion of the excess risk that is due to the presence of both the intervention and the moderator simultaneously. Significant or large interaction terms suggest that intervention effects differ by subgroups of the moderators. We will then perform stratified subgroup analyses to further investigate and describe heterogeneity between groups of individuals.

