### Measures

At all major assessment visits, participants complete interviewer-administered assessments of HIV and PrEP knowledge, perceived HIV risk, PrEP interest and self-efficacy, and patterns of substance use, sexual behaviors, physical and psychosocial health conditions, and health service utilization. Socio-demographics (e.g., race/ethnicity, age) are assessed at baseline only. Medical record review is conducted throughout the course of the study. Biological measures of adherence to oral PrEP (i.e., concentrations of tenofovir in hair samples [70, 71]) are collected at 3-, 6- and 12-month follow-up visits only, and incident HIV infection is assessed at 12-month follow-up visits only (Table 1). Because a long-acting injectable PrEP medication has recently been approved for prescribing among people who have sexual exposures to HIV, [71–74] some participants might use this newer formulation instead of oral PrEP medications. For participants who use injectable PrEP, which must be administered by a healthcare professional, we will track adherence using medical and pharmacy records, as biomarkers of adherence to injectable PrEP are not available and may not provide additional information on adherence beyond review of medical and pharmacy records.

Co-primary outcome measures: Our first co-primary outcome, PrEP uptake, is primarily assessed via visual confirmation that a PrEP prescription was filled and received. At each follow-up assessment, we also request that participants bring in their PrEP prescription packaging to confirm that the prescription was picked up. For injectable PrEP, uptake will be defined as receipt of their first injection,

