Conceptual mediators: Informed by our preliminary studies, conceptual mediators of intervention effects are measured by self-report at each major assessment visit and include HIV knowledge (assessed using selected and adapted items from the International AIDS Questionnaire [78] and the Marsch HIV/AIDS knowledge test [78, 79]), perceived HIV risk (using items adapted from the validated Perceived Risk of HIV Scale [80]), and PrEP knowledge, interest, motivation, and behavioral skills (using items adapted from research with people who use drugs [81]). PrEP use intentions and self-efficacy are measured using selected and adapted items from work by Walsh, [82] and anticipated PrEP stigma from work by Calabrese, et al. [83]. Structural barriers to PrEP access include healthcare access and utilization (items from the National HIV Behavioral Surveillance Survey [84]) and stigma from medical providers (from Fong, et al. [85]).

Epidemiologically linked moderators: Also based on our formative research, we hypothesize observing heterogeneity in intervention effects according to participant age, gender, and baseline sexual risk (specifically, condomless vaginal or anal sex) and polysubstance use (including stimulants), assessed by self-report at baseline and follow-ups assessment visits.

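### The uptake co-primary is tested with a covariate-free chi-square although likely predictors of uptake are measured in everyone before randomisation: a modest, avoidable loss of precision, not a bias

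*Protocol article*

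**What the plan says.** Under Statistical analyses, Aim 1, the test for the first co-primary outcome is fixed: "For PrEP uptake, we will perform chi-square tests to examine group differences in proportions over the course of the study". The same sentence adds "Cox proportional hazard models to assess differences in time to PrEP initiation". Neither analysis names a baseline covariate. The regression sentence that follows the adherence text, "We will use generalized linear models (GLMs) with properly chosen link functions", names none either. The only stated use of baseline variables around the main comparison is a balance check: "We will examine the equivalence of the random assignment with regards to key baseline characteristics, including socio-demographics and risk behaviors".

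Under Measures, at every major visit "participants complete interviewer-administered assessments of HIV and PrEP knowledge, perceived HIV risk, PrEP interest and self-efficacy". In the paragraph on conceptual mediators, "PrEP use intentions and self-efficacy are measured using selected and adapted items", and the mediators are said to be measured at each major visit. Timing of assessments places the baseline visit before randomisation. Randomization is done within site.

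The Background links low uptake to low perceived risk and to limited knowledge of and interest in PrEP. It bases the intervention on motivation and self-efficacy as drivers of behaviour.

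**The concern.** Uptake has no useful baseline value of its own, because Table 1 admits only people who have never used PrEP or who stopped more than six months ago. The nearest pre-randomisation predictors are the interest, intention and self-efficacy scores, and the trial already collects them. A two-by-two chi-square cannot use them, so whatever part of the variation in uptake they explain stays in the error term. The interval around the uptake difference is then wider than the data allow, and power is lower than it could be with the same participants. This matters most if the true effect is smaller than planned, where power is no longer comfortable.

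**Working it through.** **Inputs from the documents.** Uptake 25% in control and 50% under intervention, 80 completers per arm, 90% power (Sample size calculations); two-sided alpha 0.05 (Statistical analyses); 1:1 allocation (Overview of study design).

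**Assumed input.** The correlation rho between the baseline score and uptake. The documents give none, so a range is shown.

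**Step 1: reproduce the plan's figure.** With n per arm, p = mean of the two rates:
- SE under the null = sqrt(2 × p(1 − p)/n) = sqrt(2 × 0.375 × 0.625/80) = 0.0765
- SE under the alternative = sqrt((0.25 × 0.75 + 0.50 × 0.50)/80) = 0.0740
- z = (0.25 − 1.96 × 0.0765)/0.0740 = 1.35, so power = 91.2%

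The stated 90% is met. Enrolment also follows: 80/0.8 = 100 per arm, 200 in total.

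**Step 2: effect of adjustment.** To a good approximation, adjusting for a score with correlation rho multiplies both standard errors by sqrt(1 − rho²). This is worth 1/(1 − rho²) times as many participants. Example for rho = 0.4: sqrt(0.84) = 0.917; z = (0.25/0.917 − 0.150)/0.0740 = 1.66; power = 95.2%.

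| Assumed rho | Equivalent sample size | Power, 25% v 50% | Gain | Power, 25% v 45% | Gain |
|---|---|---|---|---|---|
| 0 | 1.00 | 91.2% | – | 76.0% | – |
| 0.2 | 1.04 | 92.2% | 1.0 | 77.7% | 1.7 |
| 0.3 | 1.10 | 93.5% | 2.3 | 79.9% | 3.9 |
| 0.4 | 1.19 | 95.2% | 4.0 | 83.0% | 7.0 |

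The 45% scenario is not in the plan. It shows a smaller effect than the one planned for.

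**Step 3: interval width at the planned effect.** The unadjusted 95% half-width is 1.96 × 0.0740 = 14.5 percentage points. At rho = 0.4 it is 14.5 × 0.917 = 13.3 points; at rho = 0.2 it is 14.5 × 0.980 = 14.2 points.

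**Step 4: check by simulation.** The adjusted analysis was a logistic regression on arm and one baseline score, standardised to a marginal risk difference with an influence-function standard error. It was compared with the plain chi-square at 80 per arm, with 3,000 to 4,000 trials per setting. Site was not simulated.

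| Odds ratio per SD of score | Variance ratio, chi-square over adjusted | Power 25% v 50%, chi-square → adjusted | Power 25% v 45%, chi-square → adjusted |
|---|---|---|---|
| 1.0 (not prognostic) | 0.99 | 91.5 → 91.9% | 78.0 → 78.4% |
| 1.65 | 1.05 | 91.4 → 92.8% | 74.5 → 76.2% |
| 2.0 | 1.10 | 91.0 → 93.4% | 76.7 → 80.0% |
| 2.7 | 1.18 | 91.0 → 94.6% | 75.6 → 82.9% |

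Odds ratios of 1.65 to 2.7 correspond to correlations of about 0.2 to 0.4, so the simulation agrees with the formula. In these settings the type I error of the adjusted test was 5.0% to 5.5%. With a non-prognostic score there is no real gain and practically no loss.

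**The case against.** The case against is substantial, and much of it stands.

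- *The test is not wrong.* A chi-square on a randomised binary outcome is valid and unbiased, and it matches the basis of the sample size. This stands: preferring an adjusted estimator is a matter of efficiency.
- *Covariates may be left to the analysis plan.* This is an article, and the article nowhere says that adjusted analyses are excluded. A reader might infer a deliberate decision against adjustment, which the text does not support. It does, however, fix a named test for this outcome, and that test cannot carry a covariate. The point concerns that stated choice and does not treat silence as an omission.
- *Regression is already foreseen.* The Cox model can carry covariates, and Aim 3 adds an interaction term to the Aim 1 analyses. Neither names a baseline adjustment. The Aim 3 term cannot be placed in a chi-square, so a regression form for uptake is needed in any case.
- *The gain rests on an assumption and may be small.* This stands. Interest and perceived risk are described as low, which may restrict their range. Access barriers are not captured by intention. The intervention aims to change motivation after baseline, which may weaken the link in that arm.
- *Chance imbalance.* With 80 per arm, a difference of at least 0.2 SD in a baseline score arises in about 21% of trials (0.2/sqrt(2/80) = 1.26, two-sided). A reader might infer that the unadjusted estimate is therefore unsound. It is not: the unadjusted standard error and type I error already allow for such imbalance.

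**Conclusion.** The concern holds as a small matter of efficiency. The planned test ignores likely predictors of uptake that are measured in everyone before randomisation. At assumed correlations of 0.2 to 0.4, this forgoes about 1 to 4 points of power at the planned effect and about 2 to 7 points if intervention uptake is 45%. The correlation is an assumption throughout. The documents support prognostic value only in qualitative terms.

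Two stronger readings are not supported. The first is that the uptake comparison is biased or underpowered: it is unbiased, and it has 91.2% power on the plan's own inputs. The second is that the gain is large. At a correlation of 0.5, power would be 97.0% at the planned effect and 87.0% at 45% uptake, but that needs a very strong predictor: in the simulation an odds ratio of about 3.7 per SD still fell slightly short of it.

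**What to change.** Before any comparison by arm:

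1. Make the primary uptake analysis a logistic regression on arm, site (the randomisation factor) and one named baseline score, for example PrEP use intention. Standardise over the sample to a marginal risk difference, with a robust or bootstrap standard error.
2. Name the single score and its scoring in advance, since several related constructs are measured. Use the baseline value only: later values are treated as mediators of the intervention effect, and adjusting for them would remove part of that effect.
3. Add the same terms to the Cox model for time to initiation.
4. Keep the chi-square as the supporting unadjusted analysis.

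The cost is wording in the analysis plan. No new data, visits or participants are needed. The downside is a slightly more complex primary analysis and one or two degrees of freedom if the score proves weak.

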## Methods

### Overview of study design

PrEP for Health is a two-arm RCT aiming to enroll 200 HIV-negative PWID attending two SSPs in MA (n = 100 per site). Based on the locations of recent HIV outbreaks and clusters among PWID, we partnered with two SSPs (i.e., study sites) in Lawrence and Boston/Cambridge, MA, jurisdictions heavily affected by opioid and stimulant use and injection-related HIV transmission. The SPIRIT figure of this trial, including the schedule of screening, enrollment and follow up visits, is illustrated in Fig. 1. In brief, participants are randomized 1:1 to receive the PrEP for Health intervention or an enhanced standard of care (eSOC) control condition, as detailed below. Participants are then followed for 12 months with major assessment visits scheduled at baseline and 1-, 3-, 6-, and 12-month follow-up timepoints. Participants receive escalating incentives across these assessment visits (ranging from $20-$50). Participants randomized to the PrEP for Health intervention also receive $10 for each of two primary intervention sessions. Participants provide written informed consent (described below). All study materials described in the sections below are available in English and Spanish (following professional translation and verification by bilingual research personnel). The Fenway Health institutional review board (IRB) reviewed and approved all study protocols. The following description of the protocol is based on Version 1.7, most recently updated and approved on 10/26/2022.

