### Randomization

Following baseline assessments (see Fig. 1 and Measures section below for details), participants are randomized into either of the two study arms using a pre-programmed randomization module in REDCap. Randomization is site-specific to ensure balance within site. After randomization, participants randomized to the PrEP for Health intervention condition can elect to have their initial intervention session with the PrEP Navigator that day or schedule an appointment for a later date.

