Second, to enhance scalability if PrEP for Health is found to be efficacious, we designed a rigorous yet “real-world” intervention to help maximize widespread implementation. Our study takes place in two distinct sites in terms of inner (i.e., organizational) and outer contextual (i.e., community) factors. While our intervention and assessment procedures are identical across sites, we worked with our SSP research partners to develop recruitment and retention protocols to maximally engage participants in the study; while we use most of our recruitment and retention activities in both sites, differences in the communities (e.g., in terms of urban density, availability of public transportation options) have required regular reconsideration of which strategies to prioritize in each site. By being in constant community with our SSP research partners through regular all-team meetings and daily interactions with study staff, we have also been able to improve our referral processes, for example, by ensuring that staff are present on days when PrEP prescribers are onsite or in nearby mobile clinics. Maintaining flexibility in some aspects of our approach based on our understanding of real-world organizational and community factors (e.g., changing our study schedule to be present on days when mobile clinics are nearby) has supported implementation of the trial so far.

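### Randomisation is by site, but the chi-square named for the uptake co-primary does not use site; the test is valid but slightly conservative if uptake differs between sites (minor, free to fix)

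*Protocol article*

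**What the plan says.** All of this is in the protocol article.

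- Randomization: "Randomization is site-specific to ensure balance within site". The design overview gives 1:1 allocation and plans 100 participants at each of two sites.
- Statistical analyses, Aim 1: for uptake, "we will perform chi-square tests to examine group differences in proportions over the course of the study", plus Cox models for time to initiation. Site is not mentioned for either. The general rule is "All analyses will use two-tailed tests of significance, with significance at alpha level 0.05".
- Sample size calculations: control uptake 25%, intervention uptake 50%, and "we need 80 completers per condition to have 90% power to find a significant difference at alpha = 0.05". Allowing for 20% attrition gives 200 enrolled.
- Discussion: "Our study takes place in two distinct sites in terms of inner (i.e., organizational) and outer contextual (i.e., community) factors". The differences it goes on to name are urban density and public transport, in connection with recruitment and retention. No uptake rate by site appears anywhere.

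**The concern.** When arms are balanced within site, a difference in uptake between sites affects both arms equally and cannot move the arm difference. A chi-square on the pooled 2×2 table does not know this. It takes its variance from the overall uptake proportion, which includes the between-site spread. The standard error is then larger than the true sampling variability, the test rejects less often than its nominal level, and some power is given up. An unstratified confidence interval for the risk difference would be too wide for the same reason.

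Uptake is the co-primary outcome on which the sample size rests, and site is the only stratification factor the article describes. Carrying it into the test is standard practice.

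**Working it through.** **Inputs.** From the article: two sites of 100, 1:1 allocation within site, 25% v 50% uptake, two-sided alpha 0.05, 80 completers per arm, 20% attrition. This gives about 40 completers per arm per site. Assumed: a between-site gap g in uptake, ranged from 0 to 40 percentage points, with the same risk difference at both sites and equal numbers in each cell.

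**Step 1: the plan's own figure.** Mean uptake is 0.375.

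- n per arm = [1.96·√(2·0.375·0.625) + 1.2816·√(0.1875 + 0.25)]² / 0.25² = (1.342 + 0.848)² / 0.0625, which rounds up to 77.
- With 80 per arm, the null SE is √(0.375·0.625·2/80) = 0.0765 and the alternative SE is √(0.4375/80) = 0.0740. Power = Φ[(0.25 − 1.96·0.0765)/0.0740] = 91.2%.
- 80/0.8 = 100 per arm.

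The stated 80 per arm for 90% power is therefore reproduced, with a mild round-up, as an unstratified two-proportion calculation.

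**Step 2: type I error of the plain chi-square.** With uptake 25% in both arms, the chi-square uses a variance of 0.25·0.75 = 0.1875. The mean within-site variance is 0.1875 − (g/2)².

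- g = 20 points (15% and 35%): 0.1775, ratio 1.056, SE ratio 1.028. The effective critical value is 1.96·1.028 = 2.014, so type I error is about 4.4%. Simulation (300,000 replicates) gives 4.6%.
- g = 40 points (5% and 45%): 0.1475, ratio 1.271, SE ratio 1.127. The effective critical value is 2.21, so type I error is about 2.7%. Simulation gives 2.9%.
- g = 10 points: simulation gives 5.0%.

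CMH stays at 5.0% at each of these gaps.

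**Step 3: power at 25% v 50%.**

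- The null SE used by the plain chi-square stays at 0.0765.
- The null SE used by the stratified test is √[(2/80)(0.2344 − (g/2)²)].
- The true SE of the difference is √[(0.4375 − 2(g/2)²)/80].

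At g = 20 points the last two are 0.0749 and 0.0722. Power is then Φ[(0.25 − 1.96·0.0765)/0.0722] = 91.7% for the plain test and Φ[(0.25 − 1.96·0.0749)/0.0722] = 92.3% for the stratified test. Simulated values:

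| Site gap | Plain chi-square | Site-stratified CMH | Loss |
|---|---|---|---|
| 0 | 91.1% | 91.1% | none |
| 10 points | 91.2% | 91.5% | 0.3 |
| 20 points | 91.6% | 92.6% | 1.0 |
| 40 points | 93.2% | 95.8% | 2.6 |

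The plain test's power rises with the gap because the true SE falls while its rejection threshold stays put. What is lost is the further gain that stratification would bring.

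**Step 4: confidence interval.** The unstratified SE of the risk difference exceeds the stratified one by 0.6%, 2.4% and 10.6% at gaps of 10, 20 and 40 points.

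**Step 5: a smaller effect.** At 25% v 40% (an assumption, not in the article), simulated power is 53.5% v 54.8% at a 20-point gap and 53.5% v 61.6% at 40 points, a loss of 1.3 and about 8 points.

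**The case against.** The strongest reply is that nothing here damages the trial's inference. The plain chi-square is valid, it errs on the safe side, and at the planned effect it keeps more than 90% power at every gap tried. For gaps up to 20 points the loss is about 1 point or less. All of that stands, and it is why the point is minor.

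It is also fair that the article says only chi-square tests, which does not rule out a stratified version, and that an analysis plan not shown here may name one. If it does, a cross-reference is enough. As written, though, the ordinary reading is a pooled Pearson test.

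Two stronger readings are tempting, and the article does not support either:

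- **That the sites are known to differ in uptake or in access to prescribers.** The Discussion names density and transport as differences. It mentions prescribers only in a general remark about referrals, and says intervention and assessment procedures are the same at both sites. Different settings need not mean different uptake, and only a difference in uptake matters here.
- **That the adherence GEE has the same fault.** Adherence is assessed only among participants who report starting PrEP, a subset formed after randomisation, so balance within site is not guaranteed there and the mechanism above does not carry over. Covariate lists for the models are also commonly left to the analysis plan.

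**Conclusion.** The point holds as a minor one. The uptake test named in the article does not use the factor by which participants are randomised, and this makes it conservative to the extent that uptake differs by site. At the planned effect the cost is nothing with no gap, about 0.3 points of power at a 10-point gap, 1.0 at 20 and 2.6 at 40. It becomes material only if the gap is large and the true effect falls short of 25 points.

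A reader might infer that the trial is underpowered or that its type I error is not controlled. Neither follows: the 90% claim is met throughout, and ignoring site pushes the error rate down, not up.

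The figures rest on an assumed gap, a constant risk difference, equal site sizes and arms that stay balanced within site among completers.

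**What to change.** State that uptake will be compared with a Cochran-Mantel-Haenszel test stratified by site, and report a site-stratified risk difference with its 95% confidence interval. For consistency, stratify the Cox model for time to initiation by site.

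The cost is a sentence or two, fixed before outcome data are analysed. Site is already recorded, there are only two strata of about 40 completers per arm, and CMH gives up nothing if the sites turn out alike (91.1% for both tests). No change in sample size is needed. Settling it in advance also removes any later choice between a stratified and an unstratified result.
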